#### Simple reaction time of the dominant hand

Handedness of the participants is determined on the basis of self-report. The participant sits in front of a computer screen holding a button in their dominant hand and reacts to the appearance of visual prompts on the screen by pressing the button. A series of 11 prompts are shown in sequence. The time period between the response to one prompt and the appearance of the next prompt ranges from 0.5 to 4 s in a random although set sequence. The outcome variable for this test, the mean reaction time, is the average length of time between the appearance of each of the last 10 prompts and the button pressed in response to that prompt.

#### Simple reaction time of the dominant foot

This test is the same as the test with the dominant hand (previous paragraph), except that the participant’s response to the visual prompt is made by pressing a pedal with the dominant foot.

#### Choice reaction time

This is a reaction time test involving both hands and both feet. The participant sits in front of a computer screen with a button in each hand and each foot resting on a pedal. A set of 41 prompts appear sequentially on the screen. The position of the prompt on the computer screen, as well as text within the prompt, indicates which hand or foot should be used in response to each prompt. If the prompt is in the upper left corner, the subject presses the button with their left thumb. If the prompt is in the upper right corner, the subject presses the button with their right thumb. If the prompt is in the lower left corner, the subject presses the left foot pedal, and if the prompt is in the lower right corner, the subject presses the right foot pedal. There is a 1-s interval between the press of a button or pedal in response to a prompt and the appearance of the next prompt. If the wrong button or pedal is pressed, the software still goes on to the next prompt, but keeps track of how many incorrect responses were made and which ones were incorrect. The outcome variable for this test, the mean reaction time, is the average length of time between the appearance of each of the last 40 prompts and the press of a button or pedal in response to that prompt. However, the reaction times corresponding to incorrect choices are not included in the mean, in accordance with the protocol described by Whelan [26]. The number of incorrect choices is also provided.

#### Response time involving the dominant hand (the Fitts’ law test)

In this test, participants perform a computerized, simple target-acquisition task (known as a Fitts’ law task) to investigate their response times using a mouse with their dominant hand. The participant completes a block, a series of target selections on a computer screen, by working through 32 trials. That is, 32 pairs of “hits” – meaning the mouse is clicked when the cursor is inside each of two circles that make up a pair. When a pair is completed, the screen goes blank. The participant can then click the mouse with the cursor anywhere on the blank screen to begin the next of the 32 pairs in that block. This process continues until all 32 pairs of that block have been completed.

The two circles of any given pair are always of equal size, although the size varies in a random but set manner from pair to pair (W in Fig. 2) as does the orientation of the circles on the screen (the angle θ in Fig. 2). The distance between the centers of the two circles (D in Fig. 2) is always the same for every pair.

**Fig. 2 Fig2:**
[figure not shown]
Computer screen used with the Fitts’ law test. The participant moves the cursor from one circle to the other and back. The process is repeated for 32 pairs of circles of different size and orientation

The participant is given a practice block of five trials before completing this task in order to become familiar with the process involved. The measured outcome from this task is the sum of the times required to complete each of trials (pairs) in a 32-trial block. The time elapsed between pairs is not counted.

#### Response time involving whole body movement (t-wall)

Participants stand in front of the t-wall, a commercially available device (Motion Fitness, Rolling Meadows, IL, USA) with a 4 × 8 bank of square buttons each of which is 8 cm per side (Fig. 3). When the test begins, one of the buttons will light. The participant hits that button with either hand. The light inside that button then goes out and another button lights until hit. This process continues for a random sequence of 100 buttons. When the last button is hit, all the buttons flash once to indicate that the test is complete. Participants are given a practice run on the t-wall to familiarize them with the process and the amount of force required in order to constitute a hit on any of the buttons. The starting position is standing an arm’s length way from the center of the device. Initially, the first button of the 100 sequence is lit. However, the timing does not begin until the participant hits that first button. The measured outcome from this test is the time from when the first button is hit to when the last button in the random but set sequence of 100 buttons is hit.

**Fig. 3 Fig3:**
[figure not shown]
The t-wall. The participant goes through a random sequence of striking 100 lighted buttons, one immediately after the other

#### Sequence of biomechanical testing

The tests for each of the five reaction and response time outcome measures are given three times on each of the three different visits. Two different random but set sequences of prompts, designated A and B, are used for each of the five tests. This is done to prevent the participants from memorizing the sequence of prompts and, therefore, being able to anticipate the next prompt.

Although the five tests are all given at visit 1, it is only for practice – the data is not used in the analysis of the study. This allows the participants to become familiar with each test in preparation for the two assessment visits. The sequences of prompts as used at visit 1 are alternated for the three repetitions of each of the five tests using the pattern of A, B, A.

During visit 1, a video explaining the use of the t-wall is shown to the participant. The participant is then given the chance to hit a few buttons before actually beginning the test. This allows the participant to experience how much force is required when hitting a button in order to make the light go out. Once comfortable with this concept, the participant goes through three repetitions of the 100-button test. Next, the participant is shown a second video about performing the Fitts’ law test, followed by a sample Fitts’ law test of five pairs of circles. Once the participant feels able to do the test smoothly, three repetitions of that test are completed with 32 pairs of circles in each repetition of the test. After completion of the Fitts’ law tests, a third video is shown that explains and demonstrates the hand and foot simple reaction time tests and the choice reaction time tests. The participant then performs three repetitions of each of those three tests. This denotes the completion of visit 1.

The first assessment is done during visit 2 and the second assessment is done 10 days later during the final visit. For each assessment, the five different biomechanical tests are given in the same sequence as they were practiced at visit 1. This includes showing the instructional videos before the relevant type of test but does not include doing the brief sample before performing the t-wall and Fitts’ law tests. First, two repetitions of each test are performed. Then, the participant receives either a CMT or, for those in the wait-list control group, a 10-min break. After the CMT (or break), a third repetition of each type test is given – with the five tests being given in the same order. For these two assessment visits, the two sequences of prompts for each of the five tests and the CMT are given in the order of B, A, CMT/break, A. The videos are not shown again for the tests that are completed after the CMT or break.

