There have been two changes in the eligibility criteria since this study began. Originally, the upper age limit was set at 45 years. However, as recruitment progressed it became apparent that SOF included members over the original age limit with an interest in the study. Consequently, it was decided to allow those who were still active in SOF to participate with no upper age limit. The second change allowed women to participate in the study. Initial study recruitment was limited to personnel who were not only in SOF, but were also special forces-qualified – a subset of SOF personnel who could not be female. In order to meet the required rate of recruitment, it was necessary to broaden the scope of eligibility to include members of the Special Operations Aviation Regiment who are on flight status, which includes female pilots. Both changes were approved by all IRBs involved in this study. The changes were made after 41 participants had been enrolled in the study.

### Between visit 1 and visit 2

The data from visit 1 is entered into STaRS. If all eligibility criteria are met, the participant is randomly allocated to either the treatment group or the wait-list control group. Group assignment is done using concealed allocation in a 1:1 ratio by a predetermined, computer-generated, restricted randomization scheme with random block sizes of 2, 4 or 6. The site PM has no knowledge of any details of the randomization process but accesses the group allocation module within STaRS to retrieve the participant ID and assigned group. The group assignment and date, time, and study participant ID are stored in the Structured Query Language (SQL) database. If the STaRS database is unable to be accessed when a participant needs to be allocated to a group, there is a backup allocation protocol consisting of predetermined sequentially numbered, opaque envelopes. Once allocation has been made to either the treatment group or the wait-list control group, the participant is called or sent a text message specifying their group assignment. Personnel at the PCCR who process the raw data are blinded to which group individual participants have been allocated to and will remain blinded until after completion of the study.

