### Data management and security

There are 12 Excel files that are generated during each visit in which data are collected. Those files are later combined into a single zip file. Consequently, there are three zip files created for each participant - each one containing the 12 Excel files from one of the visits. Once a zip file is created following a visit, it is uploaded into the STaRS system.

At the PCCR, the zip file is downloaded from STaRS and stored on a secure file server on the PCCR network. All PCCR servers reside behind a state-of-the-art firewall with permissions determined by Active Directory. Through the use of a custom-developed macro in Excel, the individual data points are taken from each Excel data file and copied into a single large Excel file that acts as a database containing all of the data from all of the Excel data files. There is a separate sheet in the database file for the data of each type of test that generates an Excel data file: simple hand reaction time, simple foot reaction time, choice reaction time, and Fitts’ law data. In addition, there is a fifth sheet that also contains the choice reaction time data, except that in that sheet there are blanks instead of data for those choices that were incorrect. For example, in the case when the test presented a prompt that called for a response with the left hand, but the participant used the left foot instead of the left hand. Generating a sheet of the choice reaction time data in this manner provides the opportunity for that data to be analyzed excluding times from incorrect choices, as described by Whelan [26].

There is one line created in the database file for each repetition of each type test with all of the data from that test. That line also contains the participant ID, visit number (1, 2, or 3), the type of test, which repetition of the test for that visit (1, 2, or 3), the date the test was given, and the name of the data file from which this particular set of data originated. In addition, the sheets for the choice reaction time test also include the number of incorrect choices that were made on that instance of the test.

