### Statistical methods

An intention-to-treat approach, in which participants will be analyzed according to their original treatment allocation, will be used. All observed data will be used in the analyses. Data analyses will be performed using SAS. The level of significance will be set at 0.05. Descriptive statistics of participant baseline characteristics, the reaction and response times and the PROMIS-29 scales at visit 1 will be presented for each treatment group.

The primary analyses compare the mean changes in reaction and response times from sequence A, performed before CMT/break at visit 2, to sequence A performed before CMT/break at the final visit between the treatment and wait-list control groups, using an analysis of covariance controlling for age, for each of the five biomechanical tests. Residual plots will be used to assess the validity of the model assumptions. If group variances are heterogeneous, we will use a mixed-effects regression model. If the data is non-normal, we will explore data transformations. Mean differences between groups, adjusted for age, will be reported with 95 % confidence intervals.

The secondary analyses will compare the immediate changes in sequence A before CMT/break to sequence A after CMT/break at both visit 2 and the final visit using the same methods described above.

Although we do not expect changes in the PROMIS-29 Health Survey scales or medication use in this short time frame, we will explore it by analyzing changes from visit 1 to the final visit.

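### The primary models adjust change for age only; the visit 2 starting time should be a covariate, and the visit 1 practice time, the only outcome measurement made before randomization, need not be excluded beside it

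*Protocol article*

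**What the plan says.** All references are to the protocol article.

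- *Sequence of biomechanical testing*: each of the five tests is run three times at visit 1. The prompt sequences "are alternated for the three repetitions of each of the five tests using the pattern of A, B, A", so the first and third runs use sequence A. The article describes this visit as practice and says "the data is not used in the analysis of the study".
- *Between visit 1 and visit 2*: "If all eligibility criteria are met, the participant is randomly allocated to either the treatment group or the wait-list control group". Afterwards "the participant is called or sent a text message specifying their group assignment". Visit 2 testing therefore happens with the group known but, for the runs that start the change score, before any treatment.
- *Statistical methods*: the primary outcome is the change between the sequence A runs made before CMT/break at visit 2 and at the final visit. The groups are compared "using an analysis of covariance controlling for age, for each of the five biomechanical tests". No starting time is named as a covariate.
- *Discussion*: the analysed repetitions are limited to those on either side of CMT/break, which again leaves visit 1 out.
- *Data management and security*: results are stored by visit and repetition, visit 1 included.
- *Statistical methods* also appears to list visit 1 reaction and response times among the descriptive statistics shown by group. That sits awkwardly with the statement that visit 1 data are not used.

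**The concern.** Visit 1 is a learning visit, so its times are a poor outcome and a poor start for a change score. A covariate has a different job: it need only predict the outcome within groups. A time recorded before allocation cannot systematically favour either arm, however much learning it contains. The stated reason for the exclusion therefore does not reach this use.

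The plan also enters no starting time as a covariate at all. Subtracting the visit 2 time fixes its coefficient at minus one, which is not the most precise weight unless the two times are almost perfectly correlated. Each analysed time is a single repetition, so noise in the visit 2 run passes in full into the change.

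At stake is the width of the five primary confidence intervals, using data already collected.

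**Working it through.** **The plan's own figure.** *Sample size* gives 100 evaluable participants (50 per group) with at least 85% power, raised to 120 for up to 15% loss. 100/0.85 = 117.6, so 118; and 120 × 0.85 = 102. The 120 is reproduced. The pilot standard deviations are not given, so the 85% cannot be checked directly. At two-sided 0.05 (sidedness assumed) it implies a standardized difference of (1.960 + 1.036) × √(2/50) = 0.599. That is the starting point for the power figures below.

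**Inputs that the article does not give.** Correlations between visit 1 (V1), visit 2 (V2) and the final visit (F) are assumed, with equal variances set to 1. They are read as the correlations left after age.

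**Formulas for residual variance**

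- Planned change score: 2(1 − r2F)
- Change with V1 only: 2(1 − r2F) − (r1F − r12)²
- Change with V2: 1 − r2F²
- Change with V1 and V2: 1 − (r1F² + r2F² − 2·r12·r1F·r2F)/(1 − r12²)
- Power: Φ(0.599 × √25/√k − 1.960), where k is the residual variance divided by the planned variance

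| Assumed (r12, r1F, r2F) | Planned | + V1 only | + V2 | + both | Cut by V2 | Further cut by V1 | Power with V2 | Power with both |
|---|---|---|---|---|---|---|---|---|
| Equal, 0.5 | 1.000 | 1.000 | 0.750 | 0.667 | 25% | 11% | 93.3% | 95.6% |
| Equal, 0.7 | 0.600 | 0.600 | 0.510 | 0.424 | 15% | 17% | 90.1% | 94.6% |
| Equal, 0.8 | 0.400 | 0.400 | 0.360 | 0.289 | 10% | 20% | 88.5% | 94.1% |
| AR(1), 0.5 | 1.000 | 0.938 | 0.750 | 0.750 | 25% | 0% | 93.3% | 93.3% |
| AR(1), 0.7 | 0.600 | 0.556 | 0.510 | 0.510 | 15% | 0% | 90.1% | 90.1% |
| AR(1), 0.8 | 0.400 | 0.374 | 0.360 | 0.360 | 10% | 0% | 88.5% | 88.5% |
| Learning (0.6, 0.55, 0.7) | 0.600 | 0.598 | 0.510 | 0.484 | 15% | 5% | 90.1% | 91.6% |
| Learning (0.7, 0.65, 0.8) | 0.400 | 0.398 | 0.360 | 0.344 | 10% | 4% | 88.5% | 89.8% |
| Learning (0.6, 0.55, 0.8) | 0.400 | 0.398 | 0.360 | 0.352 | 10% | 2% | 88.5% | 89.1% |

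AR(1) means r1F = r12 × r2F. *Cut by V2* is against the planned variance; *further cut by V1* is against the model that already holds V2.

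**Why visit 1 alone does little.** Its covariance with the change is r1F − r12, which is zero when the correlations are equal. Visit 1 can predict both times well and still not predict their difference. The reduction is 0% under equal correlations, under 1% in the learning rows and 4-7% under AR(1) with r from 0.5 to 0.9.

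**Simulation check** (10,000 trials, 50 per group, all correlations 0.7): power 85.32% with age only, 85.05% adding visit 1, 90.19% adding visit 2, 94.05% adding both.

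**The case against.** The case for leaving the plan alone is substantial. The exclusion is deliberate and explained by familiarization. It causes no bias, no inflated error rate and no misread result. The primary outcome is a change from visit 2, and visit 1 on its own hardly touches its variance. The useful gain requires a second alteration, entering visit 2 as a covariate. How much visit 1 then adds rests on correlations that the article does not give, and under AR(1) it is exactly zero. In the learning rows, which suit a practice visit best, a 2-5% variance cut narrows an interval by only about 1-2.6%.

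All of this stands as a limit on the size of the point. It does not supply a reason for the exclusion, which the article states outright rather than leaving to an analysis plan. The zero case is also a limiting one: it requires visit 2 to carry everything that visit 1 knows about the final time. Each analysed time is one repetition, and for simple reaction time it averages only 10 prompts. If true ability follows AR(1) but is measured with error (assumed reliability 0.7-0.9, correlation of true ability between successive visits 0.85-0.95), visit 1 adds a further 2.5-11.7% beyond visit 2.

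The no-bias argument belongs to visit 1 only. The visit 2 time is taken once participants know their group. But it is already in the primary outcome, so using it as a covariate changes its weight and brings in no new measurement.

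**Conclusion.** The point holds as a precision improvement, not as an error that threatens validity. Under equal correlations of 0.5-0.8, adjusting for the visit 2 time cuts residual variance by about 10-25% against the planned change score. The visit 1 time beside it adds from 0% to about 20%, or about 2-5% if learning makes it a weaker predictor. Every one of these figures is conditional on assumed correlations and equal variances.

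A reader might infer more, and the documents do not support it:

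- *That all five comparisons would be sharpened by visit 1.* No correlation is given for any test, so this cannot be asserted even for one.
- *That the change is free.* It uses two degrees of freedom per test. In the simulation, an uninformative visit 1 term lowered power by about 0.3 points.
- *That the full reduction from both times, 12-33% in the equal-correlation 0.5-0.8 and learning scenarios, is due to visit 1.* At the two ends of that range, visit 2 alone supplies 10 of the 12 points and 25 of the 33. Only with high equal correlations is visit 1 the larger part (at 0.8, visit 2 gives 10 of 28).
- *That visit 1 time is the only prognostic measurement fixed before allocation.* Age, PROMIS-29 and medication use are too. It is the only *outcome* measurement so fixed.
- *That visit 1 data are kept out of everything.* They are kept out of the comparisons, but *Statistical methods* appears to present them descriptively.

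**What to change.** Before unblinding, and with the date recorded:

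1. In *Statistical methods*, pre-specify three covariates for each of the five primary models: age, the visit 2 sequence A time before CMT/break on that test, and the visit 1 third-repetition sequence A time on that test. Do not enter visit 1 without visit 2.
2. In *Sequence of biomechanical testing*, say that visit 1 times are not used as outcomes or as the start of a change score. Align the matching sentence in *Discussion*. This also reconciles the exclusion with the descriptive presentation of visit 1 times.
3. State a rule for an unusable visit 1 run. Imputing the overall mean of the covariate, ignoring group, is enough.

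The cost is a few sentences, two model terms and two degrees of freedom per test. No new data are needed. With the visit 2 time in the model, the group difference is the same whether the response is the final time or the change, so the planned wording of the result can stay.

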### Software for the computer-based tests

The programs that are used for the computer-based tests were custom-developed using the Paradigm software package (Perception Research Systems, Inc.). The Fitts’ law test uses the computer mouse for the participant to interact with the program. The reaction and response time tests use hand-held buttons and foot pedals for the participant interaction. The MP150 Data Acquisition System (BIOPAC Systems, Inc.) is used to interface the output of the buttons and pedals with the reaction time testing programs that were developed with Paradigm software.

### Data collection

Patient demographics are collected at visit 1. Health care and medication use and the PROMIS-29 are administered during both visit 1 and the final visit. A checklist is used that contains a list of each repetition of each of the five biomechanical tests in the order that they are to be given. Each test is checked off as it is completed.

Four of the five biomechanical tests that are administered to each participant are performed with the participant interacting with a computer: simple reaction time test with the hand, simple reaction time test with the foot, choice reaction time, and the Fitts’ law test. A data file, in the form of a Microsoft Excel spreadsheet, is generated by the computer each time that one of those four tests is given. Since each of those four tests is given three times during each visit, there are 12 Excel files generated for each participant (visit 1 – just for practice, visit 2, and final visit). The name of each Excel data file contains the ID of the participant, a letter indicating when that data was taken: visit 1 – for practice only, visit 2, or the final visit. Also included is the date that the data was collected in the format of yy-mm-dd, as well as a letter and a number to indicate which of the five biomechanical tests, and which repetition of that test, generated the data.

The result from each repetition of the test using the t-wall is a single number representing the time in seconds (to two decimal places) that it took a participant to complete pressing the 100 buttons that constitute a repetition of that test. That number is shown in a digital display on the t-wall device. Immediately after a repetition of the t-wall test is completed, that number is written on the checklist. Consequently, there are three numbers for the t-wall that are hand-written on the hard copy checklist during the course of each visit.

